## Statistics

The primary endpoint of the study is the occurrence of acute and intermediate radiation-induced side effects, which will be observed in randomised patient cohorts treated with photon or proton therapy in a 1:1 ratio. For photon therapy, the incidence of pneumonitis and dysphagia grade II or higher at our institution is approximately 18% and 25%, respectively, which compares favourably with incidences in the published literature [6, 7]. Using proton therapy, a reduction by a factor of 4–5 seems achievable [5]. Therefore, conservative estimates for pneumonitis and dysphagia occurrence are 4% and 8%, respectively. Assuming that the two side effects are independent, the combined fraction of expected side effects is 0.18 + 0.25 – 0.18 × 0.25 = 0.39 (39%) for photon therapy and 0.04 + 0.08 – 0.04 × 0.08 = 0.12 (12%) for proton therapy.

Using these values, the required patient number to reveal a significant difference in the occurrence of side effects between the two arms is calculated as 39. This number is based on a one-sided test of proportions with a continuity correction using a normal approximation (STATA 11.2, StataCorp LP, College Station, TX, USA, function sampsi). The significance level was set to 0.05 and the power to 0.8. A one-sided test seems appropriate since a reduced occurrence of side effects is expected from proton treatment. Assuming a 20% patient dropout the final number of patients per treatment arm is 49.

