### Recruitment, randomisation and workflow

To assess whether patients can be treated with protons, a 4D-CT will be performed to evaluate the respiratory motion of the tumour. If tumour motion is larger than 10 mm, abdominal compression or gating methods can be used and the patient will undergo a second 4D-CT scan. If the respiratory motion is still too large, the patient will be treated with photons within an observational cohort. For patients with tumour motion of less than 10 mm, the gross tumour volume (GTV), clinical target volume (CTV) and organs at risk (OAR) will be delineated. Patients are then randomised for proton or photon therapy and the respective radiation plans will be calculated. If target coverage is insufficient or doses at OAR are too high, a new treatment plan using the other modality (photons or protons respectively) will be calculated. If the other plan adheres better to the constraints, the patient is treated with the respective modality within an observational cohort. Patient reallocation to another treatment arm due to nonconformity to the constraints will be statistically handled as an event in the randomised (intent-to-treat) arm. This procedure ensures maximum patient safety while not compromising results for randomised patients. Figure 1 shows a flowchart of patient allocation to treatment arms.

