### Primary and secondary endpoints

The primary aim of the study is to show whether a reduction of acute and intermediate (i.e. late-occurring pneumonitis) radiation-induced side effects (pneumonitis and dysphagia grade II or higher scored by Common Terminology Criteria for Adverse Events CTC-AE 4.0) can be achieved using proton as compared to photon beam therapy. The primary endpoint of the study will be the occurrence of radiation-induced side effects (CTC-AE 4.0 scoring) up to 6 months after treatment or re-planning with another radiation modality due to infringement of OAR or tumour coverage constraints. Secondary endpoints contain classification of severity of early and late side effects in both groups, comparison of quality of life and of treatment outcome; furthermore, dosimetric parameters and CT alterations of normal tissues at follow-up will be compared between both groups. Quality of life will be assessed additionally by the European Organisation for Research and Treatment of Cancer (EORTC) questionnaires C30 and LC13 before and at the end of treatment and at each follow-up visit. For follow-up, patients will be interviewed via telephone 2, 4, 8 and 10 weeks after treatment based on a standardised form. Clinical follow-up examinations with additional CT or FDG-PET-CT scans are scheduled 6 weeks, 3 months and 6 months after treatment. After that, follow-up will be continued outside the trial. During therapy and at follow-up, scoring of side effects will be performed according to CTC-AE 4.0. After that, follow-up will be continued outside the trial and scoring of side effects will also be performed according to CTC-AE 4.0.

The trial design and protocol adhere to Standard Protocol items: Recommendations for Interventional Trials (SPIRIT) criteria (www.spirit-statement.org); the SPIRIT checklist and figure can be found as Additional file 1: Table S1 and Additional file 2: Figure S1.

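### The primary endpoint counts re-planning as an event, but the sample size uses toxicity rates only, so the stated 80% power is not for the endpoint as defined

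*Protocol article*

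**What the plan says.** Under *Primary and secondary endpoints*, the protocol article defines the primary endpoint as side effects up to 6 months after treatment "or re-planning with another radiation modality due to infringement of OAR or tumour coverage constraints". *Recruitment, randomisation and workflow* shows that the second component is intended: "Patient reallocation to another treatment arm due to nonconformity to the constraints will be statistically handled as an event in the randomised (intent-to-treat) arm".

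The *Statistics* section describes a narrower endpoint: "The primary endpoint of the study is the occurrence of acute and intermediate radiation-induced side effects". Its expected rates have two components each, "0.18 + 0.25 – 0.18 × 0.25 = 0.39 (39%) for photon therapy" and "0.04 + 0.08 – 0.04 × 0.08 = 0.12 (12%) for proton therapy". From these, "the required patient number to reveal a significant difference in the occurrence of side effects between the two arms is calculated as 39", using a one-sided, continuity-corrected test of two proportions. On the error rates it says: "The significance level was set to 0.05 and the power to 0.8". A 20% dropout allowance brings 39 to 49 per arm. No expected frequency of re-planning is given for either arm.

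**The concern.** A power statement holds only for the endpoint whose rates went into it. Here the rates contain no re-planning term, although re-planned patients are to be counted as events. The calculation therefore fits the defined endpoint only if nobody is re-planned, or if the two arms' re-planning rates happen to offset each other. The article states neither.

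Two things are at stake. First, the 80% power is the only justification given for the trial's size, and it may be too high or too low. Second, the composite difference mixes toxicity with planning failures. Similar re-planning in both arms shrinks the difference, and a null result could then be misread as no toxicity benefit. Re-planning mainly in the photon arm widens it, and a positive result could be read as a larger reduction in observed toxicity than occurred.

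**Working it through.** **Inputs from the *Statistics* section.** Photon: pneumonitis 18%, dysphagia 25%. Proton: 4% and 8%. One-sided alpha 0.05 (z = 1.645), power 0.80 (z = 0.842), 1:1 allocation, dropout 20%.

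**Step 1: reproduce the plan's figure.**

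- Photon: 0.18 + 0.25 − 0.045 = 0.385, rounded to 0.39.
- Proton: 0.04 + 0.08 − 0.0032 = 0.1168, rounded to 0.12.
- Difference d = 0.27, mean rate 0.255.
- Uncorrected size: n′ = [1.645·√(2·0.255·0.745) + 0.842·√(0.39·0.61 + 0.12·0.88)]² / 0.27² = 31.16.
- With continuity correction: n = (n′/4)·[1 + √(1 + 4/(n′·d))]² = 38.2, rounded up to 39.
- With dropout: 39/0.8 = 48.75, rounded up to 49.

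Both of the plan's figures reproduce; the unrounded rates also give 39.

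**Step 2: power formula at 39 per arm.** Inverting the correction gives n′ = (n·d − 1)²/(n·d²). Then power = Φ{[d·√n′ − 1.645·√(2p̄(1−p̄))] / √(p₁(1−p₁) + p₂(1−p₂))}. For 39% versus 12%, n′ = 31.94 and power is 0.809, which agrees with the plan.

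**Step 3: add re-planning.** The article gives no rate, so every rate r below is an assumption. If re-planning is independent of toxicity t, the composite rate is t + r − t·r. For example, with 10% in both arms:

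- Photon: 0.39 + 0.10 − 0.039 = 0.451.
- Proton: 0.12 + 0.10 − 0.012 = 0.208.
- The difference falls from 0.27 to 0.243, n′ = 31.20, and power is 0.66.

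| Assumed re-planning | Photon vs proton composite | Evaluable per arm for 80% | Power at 39 per arm |
|---|---|---|---|
| None | 39.0% vs 12.0% | 39 | 81% |
| 2% both arms | 40.2% vs 13.8% | 41 | 78% |
| 5% both arms | 42.05% vs 16.4% | 46 | 73% |
| 10% both arms | 45.1% vs 20.8% | 54 | 66% |
| 20% both arms | 51.2% vs 29.6% | 72 | 53% |
| 5% proton only | 39.0% vs 16.4% | 56 | 63% |
| 10% proton only | 39.0% vs 20.8% | 88 | 44% |
| 5% photon only | 42.05% vs 12.0% | 33 | 88% |
| 10% photon only | 45.1% vs 12.0% | 28 | 93% |
| 10% photon, 5% proton | 45.1% vs 16.4% | 38 | 82% |

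The planned power is kept when photon re-planning is roughly twice proton re-planning: about 9.5% against 5%, or 18% against 10%.

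**Step 4: relax independence.** Suppose overall toxicity stays at 39% and 12%, and half of the re-planned patients would have had toxicity anyway. The composite is then t + r − 0.5·r. With 10% in both arms this is 44% versus 17%, and power is 77% instead of 66%. With 5% in both arms it is 41.5% versus 14.5%, and power is 79% instead of 73%.

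**Step 5: does the dropout allowance cover it?** The 10 extra patients per arm replace dropouts, and a re-planned patient is an event, not a dropout. With no dropout at all (49 evaluable per arm) and independence, power would be 83% at 5% in both arms, 76.5% at 10% in both arms, and 54% at 10% in the proton arm only.

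**The case against.** The strongest reply is that the direction is unknown and may favour the trial. Excess dose to organs at risk is one of the two triggers for re-planning, and the article's rationale is that protons spare those organs better. Patients whose tumour motion remains too large are also removed before randomisation. On these premises re-planning could well be more common in the photon arm, and power would then be at or above 80%. This stands as far as direction goes. It does not rescue the stated power, because poor target coverage is the other trigger, either arm can be affected, and the article assumes no rate for either.

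Three stronger readings are tempting, and the article supports none of them:

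- **That the trial is underpowered.** This cannot be concluded without re-planning rates.
- **That the sample size was miscalculated.** It was not; 39 and 49 are correct for the rates used.
- **That any gain from photon-arm re-planning has nothing to do with toxicity.** Excess organ dose is a trigger, and the *Discussion* links lung dose to pneumonitis.

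That link is also why independence may overstate the loss, as Step 4 shows.

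One could add that the *Statistics* wording is shorthand and that a fuller protocol holds a re-planning assumption. The wording might be shorthand, but the 39% and 12% are built openly from two toxicities, with no term for re-planning. A fuller document would not remove the difference between the article's two endpoint statements.

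**Conclusion.** The concern holds as an inconsistency between the endpoint and the assumptions behind the sample size. Two sections count re-planning as a primary event, while the sample-size section leaves it out of both the endpoint and the rates. The 80% power with 39 evaluable patients per arm therefore belongs to a toxicity-only endpoint.

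The mismatch itself is certain from the text. The size and direction of its effect are not. Under the assumed rates and independence, power at 39 per arm runs from 44% (10% in the proton arm only) to 93% (10% in the photon arm only). Equal re-planning of 2% to 20% gives 78% down to 53%. Positive dependence between re-planning and toxicity moves the equal-rate results back towards 80%.

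**What to change.** 1. Make the endpoint statement in *Statistics* agree with that in *Primary and secondary endpoints*. Keep the composite and the intention-to-treat handling of reallocated patients.
2. State an assumed re-planning rate for each arm, with a range, and say whether re-planning is taken as independent of toxicity.
3. Recompute the expected composite rates and restate the power that 39 evaluable (49 randomised) per arm gives across that range.
4. Report toxicity alone as a supporting analysis, so that a difference driven by re-planning is not read as a toxicity effect.

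Dropping re-planning from the primary endpoint would also align the sections, but it is more than a wording change. The trial is already recruiting, the present intention-to-treat handling would be lost, and cross-over would still dilute the toxicity contrast.

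The cost is a short recalculation and revised text. No patients are added, but the restated power may be less favourable than 80%.

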## Discussion

The aim of this prospective randomised study is to evaluate whether radiochemotherapy for advanced-stage NSCLC patients with protons leads to decreased radiation-induced side effects as compared to photons. Acute side effects are of particular importance in thoracic tumour sites as compared to other radiation sites. Acute radiation toxicity is expected to decrease quality of life of cancer patients, though mostly only temporarily, and thus is currently being subordinated to potential tumour control in a curative setting. Radiation-induced pneumonitis, however, is a potentially lethal toxicity and can develop into chronic fibrosis, often causing deteriorating in patients’ long-time quality of life [8]. Exposure of the lung, and probably also the heart, to low and intermediate radiation doses is highly relevant for the development of pneumonitis and can be reduced by proton therapy (see Fig. 3 for dose distributions for IMRT and proton radiotherapy) [7]. Although there is a strong correlation between radiation dose and local control in preclinical studies and in studies using hypofractionated stereotactic radiotherapy or alternative treatment modification, in advanced disease dose escalation with photons did not translate into a survival benefit in the recently published RTOG 0617 study [2, 9–13]. It is noteworthy that in the latter study the dose escalation was performed without acceleration, even though a time factor exists for locally advanced NSCLC as confirmed by the CHARTWEL study [14]. Protons, by a better sparing of surrounding healthy tissue, may be able to increase the dose to the tumour without an increase in toxicity [15]. If the present study demonstrates a decrease in toxicity for equal-dose radiotherapy allied with protons versus photons, increasing radiation doses with protons within a clinical trial would be the next step to achieve better local tumour control, which may then also be related to increased overall survival and metastasis-free survival as shown by others [16].

**Fig. 3 Fig3:**
[figure not shown]
Dose distribution of one patient with locally advanced non-small cell lung cancer (NSCLC) planned with intensity-modulated radiation therapy (IMRT) (left) or protons (right) showing lower doses to organs at risk (OAR) by proton therapy

## Trial status

The trial is currently recruiting.

## Abbreviations

3D-CRT: three-dimensional conformal radiation therapy
4D-CT: Four-dimensional computer tomography
CT: Computer tomography
CTC-AE: Common Terminology Criteria for Adverse Events
CTV: Clinical target volume
FDG: Fluorodeoxyglucose
GTV: Gross tumour volume
Gy: Gray
iGTV: Internal gross tumour volume
IMRT: Intensity-modulated radiation therapy
MRI: Magnetic resonance imaging
NSCL: Non-small-cell lung carcinoma
OAR: Organs at risk
PET: Positron Emission Tomography
RBE: Relative biological effectiveness
